### Variables

#### Quantitative Variables

A variety of factors with potential influence on the diagnostic process will be extracted from both the EHR and other standalone databases at the 2 sites. Existing literature has provided information on factors related to patients, providers, and system-level parameters and the interactions of these parameters in the ED (eg, patient-per-provider ratio and patient length of stay), which can be explored further [8,13,24-29]. Several additional variables that can be extracted from the EHR will be under consideration. The number of unexpected ED visits could be associated with a higher risk of diagnostic error [8,25]. ED crowding is a complex issue related to both system-level and patient-level factors (complexity and acuity) [28] and is associated with an increased risk for patient safety, including treatment delays, reduced quality of care, and increased morbidity and mortality [24]. Prolonged ED length of stay correlates with increased patient mortality [27]. High workloads, lack of control, and communication failures may lead to patient safety risks [29]. Iordache et al [30] showed that direct and indirect care time together are significant discriminators between EDs because of the differences between their patient care profiles and unit characteristics. Prescribing error rates are shown to significantly increase if physicians are interrupted or are multitasking [31]. Textbox 1 provides a general overview of these 3 categories.

The three main categories of risk factors to be explored in this study.

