#### Sampling for Control

The control includes visits that do not meet the criteria for any trigger. We will include all ED visits in the two health systems for the entire study period (July 1, 2017-December 31, 2019). For each trigger-positive case, we will match a single trigger-negative encounter based on the availability of cases through a hierarchical procedure, which matches the encounters based on age group, gender, provider, the reason for visit, and the arrival date and time. This one-to-one matching of trigger-positive and trigger-negative cases will also help to eliminate the imbalance classes. To accommodate the potential heterogeneity across sites, the measurements will be reported as site-specific quartiles [24]. For patients with multiple ED or hospital visits during the study period, each record will be considered separately.

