### Conduct of the Study

#### Overview

This study aims to identify the factors that may interfere with the diagnostic process in the ED that potentially lead to missed, delayed, or incorrect diagnoses. On the basis of our previous work, we will use a series of electronic triggers (triggers) to identify ED encounters with potential diagnostic errors from the EHR database. Each trigger has a predefined set of inclusion and exclusion criteria implemented in Structured Query Language (SQL) and configured for specifications of each site in the study. Each site currently uses an Epic EHR system with minimal variations owing to its specific needs. These differences will be identified and accounted for after the focus interviews with the providers. The Epic specialists at both sites are in constant communication with the research team to apply the most accurate mapping of the factors and parameters between the 2 sites. The protocol is thought to be generalizable to other EHR systems, as we emphasize the analysis of common ED concepts rather than database variables specific to Epic. All SQL queries can be modified to match other systems (eg, Cerner) by matching concepts and keywords. Table 1 provides an initial list of 6 EHR-based triggers proposed in IDEA-LL after reviewing the literature on current triggers, surveying medical directors, and using a Delphi consensus process [32]. We will start our study with the first 3 triggers, including the unscheduled visit within 10 days resulting in admission, care escalation to intensive care unit within 24 hours, or death in the ED or within 24 hours of ED departure time. If for any reason, one or more of the triggers do not perform well, the triggers from the backup set will be used.

**Table 1 table1:** Proposed electronic trigger algorithms for identifying diagnostic errors.

Trigger algorithm			Description

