**Initial set of triggers**			
	Trigger 1: unscheduled return	Unscheduled return visit with admission within 7 to 10 days from the index ED^a^ visit.	
	Trigger 2: care escalation	Care escalation from the inpatient unit to the ICU^b^ within 6, 12, or 24 hours with ED attribution.	
	Trigger 3: death	All deaths in the ED or within 24 hours of admission—exclusive of palliative care.	

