#### Step 4: Analysis of the Relationship Among Patient, Provider-Care Team, and System Factors and the Risk of Being Trigger-Positive

##### Overview

This step aims to analyze the trigger-labeled data sets obtained from the 2 institutions using different machine learning and data mining techniques. Data mining is a prevalent and effective technique for extracting nontrivial, implicit, previously unknown, and potentially useful knowledge from large data sources [37]. Discovering significant information related to disease diagnosis from medical databases is possible by applying techniques such as ARM [22], CHAID, and CART.

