##### Chi-square Automated Interaction Detection

CHAID is a decision tree algorithm that determines splitting based on statistical tests and has been used to model the relationship between the predictor variables and the outcome variable in many medical applications, such as identifying factors influencing inpatient mortality [17]. In our study, CHAID will help answer the question “Which combination of factors leads to higher trigger-positive risk and therefore a higher relative risk of diagnostic error?” CHAID splits the target into two or more categories using an exploratory analysis of the relationship between a dependent factor and several predictor factors [39]. To see if splitting the sample based on these predictors leads to statistically significant discrimination in the dependent measure (trigger labels), various independent factors will be evaluated using the chi-square test [40]. Despite regression, CHAID is capable of illustrating variable clusters through an iterative process. Adjusted *P* value measures are used to determine the best value of the partition or the best split, and splitting on a larger chi-square statistic indicates a more significant partition.

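### For Trigger 1, the association between ED visit history and the trigger label is partly built in and cannot by itself be read as an association with diagnostic error

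*Protocol article*

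**What the plan says.** **Predictor.** Textbox 1 of the Protocol article names ED visit history as a patient factor to be explored. The section Quantitative Variables gives the reason: "The number of unexpected ED visits could be associated with a higher risk of diagnostic error". No counting window is stated there.

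**Trigger.** Table 1 defines Trigger 1 as "Unscheduled return visit with admission within 7 to 10 days from the index ED" visit. The overview under Conduct of the Study words it as "the unscheduled visit within 10 days resulting in admission" and makes it one of the three starting triggers.

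**Outcome that is mined.** Step 4 is titled "Analysis of the Relationship Among Patient, Provider-Care Team, and System Factors and the Risk of Being Trigger-Positive". The target of the rules and trees is the trigger label, not the reviewed error.

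**Matching.** Sampling for Control describes a procedure that "matches the encounters based on age group, gender, provider, the reason for visit, and the arrival date and time". Step 1 speaks of matching on demographics and on comorbidity or severity. Neither names prior ED use. Sampling for Control also keeps each visit of a patient as its own record.

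**Inference.** The section on Chi-square Automated Interaction Detection asks: "Which combination of factors leads to higher trigger-positive risk and therefore a higher relative risk of diagnostic error".

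**Validation.** Step 2 reviews a sample of charts and estimates, for each trigger, the odds ratio of error between trigger-positive and trigger-negative charts.

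**The concern.** A patient who comes to the ED unscheduled many times a year is more likely than others to have another such visit in any given 10 days, whatever happened at the index visit. If some of those visits end in admission, the index visit is labelled positive under Trigger 1. The same habitual rate determines how many visits lie in the patient's past. Predictor and label then share a cause that need not involve diagnosis at all, and an association between them is expected even if every return is captured and no error is made.

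Step 2 does not separate the two. It asks whether trigger-positive charts contain more errors, and a trigger can do well on that question while one factor predicts mainly its false positives. Those false positives gather among frequent users, so the misclassification depends on the factor and pushes its association with the label away from the null.

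At stake is the reading of one candidate factor. The Results and Discussion sections intend the findings to inform decision support, and a built-in association reported as a contributor to error would be a false lead there.

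**Working it through.** The article gives no visit rate, admission share, trigger rate or predictive value, so it has no figure to reproduce. All rates below are assumptions.

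**Step 1. Background returns only.** With visits arriving as a Poisson process, the chance that an unrelated return with admission falls in the window is

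P = 1 − exp(−visits per year × admission share × days / 365).

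With 10 days and an admission share of 0.30 for everyone:

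| Visits per year | P | Ratio to 0.5 per year |
|---|---|---|
| 0.5 | 0.41% | 1 |
| 4 | 3.2% | 7.9 |
| 6 | 4.8% | 11.7 |
| 12 | 9.4% | 22.9 |

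Example: 6 × 0.30 × 10/365 = 0.0493, and 1 − exp(−0.0493) = 0.0481. A 7-day window, an admission share of 0.20, or both, leaves the ratio at 6 per year between 11.8 and 11.9. The admission requirement thus lowers the level but not the ratio, as long as the share is the same at all visit rates.

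**Step 2. Frequent users admitted less often.** Keep 0.30 for the patient with 0.5 visits per year and lower the share for the patient with 6 per year. The ratio falls from 11.7 to 5.9 at a share of 0.15, 2.0 at 0.05 and 1.0 at 0.025. The effect can therefore vanish.

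**Step 3. Mixture with true errors.** These ratios compare single patients and count only background returns. A simulation gives the association that an analyst would see. Its assumptions are:
- 1,000,000 patients with gamma-distributed visit rates (mean 0.5 per year, shape 0.5), followed for 2.5 years.
- Each visit is a record, and one random trigger-negative record is drawn per trigger-positive record. The protocol's matching variables are not simulated.
- Error is independent of visit history, and history is coded as 4 or more visits in the prior year.
- The admission share is 0.30, either for all or lowered by 50% or 80% for patients above 3 visits per year.

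The table gives the odds ratio of high visit history for being trigger-positive. The positive predictive value (PPV) of the trigger for error is in brackets.

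| Error rate; chance that an error causes the return | Equal admission | 50% lower | 80% lower |
|---|---|---|---|
| 0; 0 | 2.69 (0%) | 1.94 (0%) | 1.40 (0%) |
| 0.05; 0.05 | 2.31 (21%) | 1.67 (24%) | 1.24 (25%) |
| 0.10; 0.05 | 2.15 (36%) | 1.62 (39%) | 1.22 (41%) |
| 0.10; 0.10 | 1.79 (51%) | 1.44 (55%) | 1.17 (57%) |
| 0.10; 0.20 | 1.55 (66%) | 1.33 (69%) | 1.13 (71%) |

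In the runs with errors, the odds ratio of history for error itself was 0.98 to 1.01, as built in. Every excess over 1 in the table is therefore spurious.

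**Step 4. Would Step 2 of the plan reveal it?** In the same runs the odds ratio of error for trigger-positive against trigger-negative charts was 5.1 to 28.2. The comparison planned in Step 2 would show a strong link between trigger and error while the association with history remained spurious.

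**The case against.** Several points on the other side carry weight.

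- **The admission condition.** An ordinary repeat visit that ends in discharge does not meet Trigger 1. If frequent users are admitted much less often, the effect is small. This stands, and it is why the range reaches down to about 1.1.
- **Matching.** Comorbidity or severity (Step 1) and reason for visit (Sampling for Control) are related to frequent use and may remove part of the difference. This stands too. The residual is unknown, and neither list fixes prior ED use itself.
- **Trigger refinement.** Criteria are refined after chart review, poorly performing triggers can be replaced, and Limitations and Strengths concedes false positives. The bias is largest when predictive value is low, which is when Trigger 1 is most likely to be changed. But with equal admission shares the simulated odds ratio is still 1.79 at a PPV of 51% and 1.55 at 66%, and the article names no method for removing false positives.
- **Exploratory purpose.** The Objective leaves causal work to aim 2, and the number of unexpected visits is only under consideration; Textbox 2 has no count of prior visits. This limits the consequences. It does not repair the step from trigger risk to error risk in the CHAID section.

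A reader might go further and infer spurious odds ratios of 4 to 12, from comparing patients with 4 to 12 visits per year against 1. That holds only if every Trigger 1 positive is background and admission shares do not vary with visit rate. A reader might also infer that visit history will be a leading split, or that its association has nothing to do with error. The article supports neither: nothing in it ranks the factors, and it cites literature for a possible real association.

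**Conclusion.** The point holds for one factor under one trigger. The association between ED visit history and the Trigger 1 label is partly built in, because both follow the patient's habitual rate of unscheduled visits and the stated matching does not hold that rate fixed. The inference from trigger-positive risk to error risk is not valid here, and Step 2 does not supply the missing test.

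The size cannot be derived from the documents. With history unrelated to error, the spurious odds ratio for 4 or more prior-year visits was about 1.1 to 2.7, depending on the trigger's PPV and on how much less often frequent users are admitted. That range rests on assumed rates and omits the matching, which may lower it. A true association may exist alongside. Triggers 2 and 3 are not defined by a return visit and do not share this mechanism.

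**What to change.** 1. State that ED visit history is counted only before arrival at the index visit, so that the return visit cannot enter the predictor.
2. For Trigger 1, do not report visit history as a risk factor for diagnostic error from the trigger label alone. Assess it against the chart-reviewed error label in the Step 2 sample, and under Triggers 2 and 3. Because charts are sampled by trigger status, weight this analysis by the sampling fractions, and allow for repeat records of the same patient.
3. As a sensitivity analysis, run the Trigger 1 query in a later window of equal length, for example days 31 to 40 after the index visit, and report the association with visit history in both windows side by side.

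The cost is one further query on data already held and two small analyses. The reviewed sample is smaller than the trigger-labelled data set, so intervals for visit history will be wider. The later window may still contain returns due to a delayed diagnosis, and subtracting its association could remove true signal. It should serve as a check and not as a subtraction rule.

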**Patient Factors**
DemographicsEmergency department (ED) visit historyComplexity and comorbidity
**Provider-Care Team Factors**
Shift schedule and workloadPatient-per-provider ratioInterruptions and trauma
**System Factors**
ED boardingEmergency severity index triage distributionTotal direct and indirect care time

#### Qualitative Variables

Qualitative analysis of the ED environments, such as the cognitive load on individual providers, is outside the focus of this study but is under exploration in another aim of this grant. However, we will study factors such as patient acuity, patient volume, waiting times, number of ED providers per shift, and number of boarded ED patients (admitted to inpatient unit but still in ED because of lack of inpatient space) in the system as proxies for some of the qualitative factors such as the cognitive load.

### Data Quality and Safety Monitoring

We will evaluate compliance with the study methodology, quality of available data, patient protection, and adherence to Good Clinical Practice guidelines. We anticipate differences in terms of practice among the sites that may impact data quality. To ensure that the practice differences are accounted for, we recruited clinicians at each site to determine important differences and help customize the trigger algorithms. In addition, data consistency and completeness will be audited using data queries designed in accordance with standard techniques. Meanwhile, potential inconsistencies and missing values will be identified during the clinician chart reviews to design and apply adequate data imputations.

The EHR systems at both sites are the same, and we use standard measurements through health systems, with some minor customizations. These standard measurements will work as proxies to better identify conditions that may result in an error, so we do not anticipate that differences in practices across sites will affect data quality. Inconsistent data will be used to examine and enhance the validity of the defined measures (triggers) and assess their performance characteristics as predictive values. Data will be screened for missing values, and most of the missing data elements will be replaced by the closest available proxy in the EHR. As both sites use Epic as their official EHR system, care providers and Epic specialists at both sites will be engaged in this discussion to accommodate potential deployment variations. In the rare event of technical problems, remaining missingness will be adequately handled by missing data techniques such as data imputation or maximum likelihood estimations [5]. Incorrect data entries in the Epic system are very difficult to identify because of the lack of other reference ground truths. However, we will perform a data cleaning procedure to ensure the meaningfulness of temporal information, and incorrect timings (such as negative values for the length of stay) will be replaced by approximations based on the follow-up events. We will also report the missing data rate and dropout rates.

### Conduct of the Study

#### Overview

This study aims to identify the factors that may interfere with the diagnostic process in the ED that potentially lead to missed, delayed, or incorrect diagnoses. On the basis of our previous work, we will use a series of electronic triggers (triggers) to identify ED encounters with potential diagnostic errors from the EHR database. Each trigger has a predefined set of inclusion and exclusion criteria implemented in Structured Query Language (SQL) and configured for specifications of each site in the study. Each site currently uses an Epic EHR system with minimal variations owing to its specific needs. These differences will be identified and accounted for after the focus interviews with the providers. The Epic specialists at both sites are in constant communication with the research team to apply the most accurate mapping of the factors and parameters between the 2 sites. The protocol is thought to be generalizable to other EHR systems, as we emphasize the analysis of common ED concepts rather than database variables specific to Epic. All SQL queries can be modified to match other systems (eg, Cerner) by matching concepts and keywords. Table 1 provides an initial list of 6 EHR-based triggers proposed in IDEA-LL after reviewing the literature on current triggers, surveying medical directors, and using a Delphi consensus process [32]. We will start our study with the first 3 triggers, including the unscheduled visit within 10 days resulting in admission, care escalation to intensive care unit within 24 hours, or death in the ED or within 24 hours of ED departure time. If for any reason, one or more of the triggers do not perform well, the triggers from the backup set will be used.

**Table 1 table1:** Proposed electronic trigger algorithms for identifying diagnostic errors.

Trigger algorithm			Description
**Initial set of triggers**			
	Trigger 1: unscheduled return	Unscheduled return visit with admission within 7 to 10 days from the index ED^a^ visit.	
	Trigger 2: care escalation	Care escalation from the inpatient unit to the ICU^b^ within 6, 12, or 24 hours with ED attribution.	
	Trigger 3: death	All deaths in the ED or within 24 hours of admission—exclusive of palliative care.	

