### Limitations and Strengths

We anticipate some difficulties and potential limitations to our forthcoming project. First, although we have based our analysis on the patients’ medical records, it is notable that this information is not always available at all sites. Our method potentially cannot be extended to EDs that do not have an integrated EHR system, as different EDs might use incompatible EHR systems to ours, which at least requires an adaptation phase. We intentionally chose the community and academic sites to learn more about the potential difference and have recruited clinicians at each site to determine important differences and help customize the trigger algorithms. We also believe that by incorporating commonly accepted and standard measurements in this study, any future translation to other health systems would be possible by a simple mapping to the database elements of the target EHR system.

Second, our approach to investigate the risk of diagnostic error for ED patients with care escalation or death within a certain period from ED discharge will not include many events, including those that occur within the same ED encounter, possible events in other hospitals, and flag records that meet trigger criteria but are not associated with diagnostic error. We will attempt to update our data exploration approach to reduce the rate of such false-positive triggers. Conversely, a strength of our study is that the simultaneous investigation of 2 separate health systems with both adult and pediatric EDs reduces the chance of biased conclusions. These limitations are balanced by several unique strengths of this study to help identify potentially associated contributory factors of diagnostic error in the ED.

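### As worded in Table 1, Trigger 2 misses ICU moves made while a patient boards in the ED, so its sensitivity falls as boarding and ED length of stay, both factors under study, rise.

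*Protocol article*

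**What the plan says.** Table 1 (Initial set of triggers) describes Trigger 2 as "Care escalation from the inpatient unit to the ICU" "within 6, 12, or 24 hours with ED attribution". It does not say when the clock starts. The Overview under Conduct of the Study words the same trigger as "care escalation to intensive care unit within 24 hours", with no origin unit. Step 1 says that the algorithms in Table 1 are the ones to be applied.

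Two other places bear on the clock. Textbox 2 lists ED discharge time, next unit and time to ICU among the Trigger 2 fields. Limitations and Strengths describes escalation or death within a period from ED discharge, and says the approach "will not include many events, including those that occur within the same ED encounter".

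Boarding is a named system factor in Textbox 1. Qualitative Variables measures it as the "number of boarded ED patients (admitted to inpatient unit but still in ED because of lack of inpatient space) in the system". ED length of stay is a listed predictor for all triggers (Textbox 2).

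On controls, Sampling for Control says: "The control includes visits that do not meet the criteria for any trigger". They come from all ED visits in the study period, one per case, by a procedure that "matches the encounters based on age group, gender, provider, the reason for visit, and the arrival date and time". The dependent variable in the mining step is the trigger label (Chi-square Automated Interaction Detection).

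**The concern.** By the article's own definition, a boarder is admitted but still physically in the ED. An ICU move from there starts neither on an inpatient unit nor after ED discharge, so on the Table 1 wording it cannot fire Trigger 2. The visit then meets no trigger, unless the patient dies and fires Trigger 3 or later fires Trigger 1, and it becomes an eligible control.

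The missed events are therefore not a random loss. The longer a patient boards, the more of the period after admission is spent where an escalation cannot count. The sensitivity of the outcome label depends on an exposure that the study sets out to evaluate. Limitations and Strengths admits that same-encounter events are missed but does not link this to boarding. Its stated remedy is to reduce false positives, whereas this is a false-negative problem. Step 2 reviews only a sample of charts, and nothing says that the review relabels the mined data.

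**Working it through.** The article gives no escalation rate, boarding share or effect size, so there is no figure to reproduce. Every rate below is an assumption used to show scale. The model is outcome misclassification with perfect specificity.

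**Patient level, among admitted patients.** Let p0 be the escalation risk without boarding, p1 the risk with boarding, and f the share of boarded patients' escalations that occur before they leave the ED and are missed.

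Observed OR = odds(p1(1 − f)) / odds(p0), where odds(p) = p/(1 − p).

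Example with p0 = p1 = 0.02 and f = 0.1: (0.018/0.982) / (0.020/0.980) = 0.01833/0.02041 = 0.90.

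Results at p0 = 0.02:

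| True OR | f = 0.1 | f = 0.2 | f = 0.33 | f = 0.5 |
|---|---|---|---|---|
| 1.0 | 0.90 | 0.80 | 0.67 | 0.49 |
| 1.2 | 1.08 | 0.96 | 0.80 | 0.59 |
| 1.5 | 1.35 | 1.19 | 0.99 | 0.74 |
| 2.0 | 1.79 | 1.59 | 1.32 | 0.98 |

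Baseline risks of 1% and 5% change these by at most 0.03. The observed OR falls below 1 only when f exceeds 1 − p0/p1, which is about 0.16, 0.33 and 0.49 for true ORs of 1.2, 1.5 and 2.0.

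**Boarding count, as Qualitative Variables measures it.** Let bH and bL be the shares of admitted patients who board when the count is high and low.

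Observed OR = odds(pH(1 − bH·f)) / odds(pL(1 − bL·f)).

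With pL = 0.02, bH/bL of 0.4/0.1, 0.6/0.2 and 0.3/0.2, and f from 0.1 to 0.5:

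- true OR 1.0 is seen as 0.99 to 0.77;
- true OR 1.2 is seen as 1.19 to 0.93;
- true OR 1.5 is seen as 1.48 to 1.16.

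**Where the bias comes from.** Missed escalations as a share of trigger-negative patients are p·m/(1 − p(1 − m)), where m is the overall missed share. For p of 1% to 5% and m of 5% to 20% this is 0.05% to 1.0%. Contamination of the controls is thus small; the bias comes mainly from events lost from the positive group. Removing the missed visits from the controls gives p1(1 − f)/(1 − p1) as the boarded odds, so the observed OR becomes the true OR × (1 − f). For a true OR of 1.0 and f = 0.5 that is 0.50 instead of 0.49. Only counting the moves as positive (f = 0) returns the true OR.

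**The case against.** The case on the other side has real force.

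- **The origin restriction is not settled.** The Overview has no origin unit, boarders are described as admitted to the inpatient unit, the SQL criteria are not shown, and Step 1 says the criteria will be refined. This stands as a reason to ask for reconciliation. It does not remove the point, because Step 1 refers to Table 1, and Textbox 2 and the limitations text fit the narrow reading.
- **The boarding variable is a count, and matching uses arrival date and time.** This stands: it dilutes the bias, as the second calculation shows. It applies less to ED length of stay, which is patient-level and, if it runs to ED departure, includes boarding time.
- **Controls come from all ED visits and are not matched on disposition.** This stands. Trigger 2 cases were all admitted, while controls may have been discharged and never boarded. That pushes boarding time and length of stay towards looking harmful, so the net direction is not established.
- **The size depends on the clock.** A reader might start the window at the admission decision and compare 8 h with 2 h of boarding, which gives apparent risk ratios of 16/22 = 0.73, 4/10 = 0.40 and 0/4 = 0 for 24, 12 and 6 h windows under constant risk. No section states that clock, and the limitations text points to ED discharge. With a window from ED departure and constant hourly risk, the label rate is the same after long and short boarding (ratio 1.0), although the events that occurred while boarding are still lost. If the risk halves every 24, 12 or 6 h, the same contrast gives 2^(−6/24) = 0.84, 2^(−6/12) = 0.71 and 2^(−6/6) = 0.50.
- **The triggers came from a Delphi consensus.** Counting moves made in the ED may include the ED team correcting itself and lower the predictive value. This argues against replacing the trigger, not against a sensitivity analysis.

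**Conclusion.** The point holds in a limited form. On the literal Table 1 wording, the sensitivity of Trigger 2 falls with boarding, and among admitted patients its association with boarding and ED length of stay is biased downward. With 10% to 50% of boarded patients' escalations missed, a true odds ratio of 1.0 would be seen as about 0.90 to 0.49 at patient level and 0.99 to 0.77 for the boarding count. These ranges rest on assumed rates and on the narrow reading of the trigger.

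A reader might infer that boarding will look protective, or that the study cannot answer its question about system factors. The documents support neither. For the boarding count, most scenarios with a true harm show attenuation without reversal. The comparison with all-ED controls may pull the other way. The problem concerns the boarding-related associations under one of three initial triggers in an exploratory analysis. It is still worth correcting before mining, because the Results section says the cohort is already labelled.

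**What to change.** 1. Reconcile Table 1, the Overview and Limitations and Strengths on the origin unit and the start of the clock for Trigger 2, and state how an ICU move made while boarding is labelled.
2. Flag, from existing admission and transfer timestamps, ICU moves made after the admission decision while the patient is still in the ED.
3. Remove flagged visits from the trigger-negative pool. This cleans the controls but, as shown above, corrects little of the bias by itself.
4. Report the Trigger 2 results for boarding and ED length of stay with and without counting flagged visits as trigger-positive, preferably among admitted patients so that disposition does not drive the contrast.
5. Add to the limitations that the loss of same-encounter events depends on boarding.

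The cost is a modest query change and one additional analysis. Some flagged moves may reflect the ED team correcting itself, so they belong in a sensitivity analysis and not in a replacement trigger.
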